## Abstract

**Background:**

Integrating music into pain treatment demonstrates significant benefits, effectively reducing subjective pain levels and perioperative opioid requirements. Currently, the relationship between the impact of specific types of music and listeners’ socio-cultural background is still unclear. This is especially relevant given that sociological research indicates that these factors can have a notable influence on music preference and perception. Current evidence suggests that individuals who choose their own music may experience greater benefits. However, additional research is needed to comprehensively grasp whether the effect of (preferred) music on pain endurance remains consistent across different socio-cultural backgrounds.

**Methods:**

In this study, a collaborative effort between medical and sociological researchers aims to investigate music-induced analgesia differentiated by socio-cultural background in healthy volunteers. Participants (n = 84) will listen to self-, and researcher-chosen music and a podcast as a control condition in a cross-over study design. The primary outcome of this study is pain endurance measured by electric stimuli of increasing intensity. Detailed sociological validated questionnaires will be utilized. Considering the notable influence of educational level on music taste formation found in previous research and its crucial role as a source of socio-cultural differentiation, participants will be stratified based on their level of education.

**Discussion:**

This experimental study represents one of the first efforts to gain a socio-culturally differentiated understanding of the therapeutic potential of music. Consequently, this could pave the way to purposefully and inclusively implement personalized music in healthcare settings.

## Trial registration

This study was registered on www.clinicaltrials.gov with the identification number NCT06008951 in August 2023.

## Background

1

Pain is an enormous global problem and is highly prevalent among hospitalized patients [1,2]. Pain causes significant distress to patients and is related to an increased risk of (postoperative) complications [3]. Despite increased awareness and advances in treatment options for both acute and chronic pain, effective pain management with minimal adverse events remains a persistent problem. In recent years, many studies have been published about the value of music as an adjuvant treatment for pain, also called music induced analgesia (MIA) [4].

Recorded music with the goal of ‘music as medicine’ has demonstrated benefits in different healthcare settings [[5], [6], [7]]. Examples include patients undergoing surgery, cancer patients and patients at the Intensive Care Unit (ICU) [[8], [9], [10], [11], [12]]. Additionally, evidence shows that listening to perioperative music lowers the requirement for analgesics such as opioids [13,14]. Currently, there are several theories on how music precisely affects the human body. These theories consider factors such as the influence on emotional brain centers, the autonomic nervous system, distraction, and the release of certain hormones such as dopamine and endogenous opioids [4,15]. Despite extensive research in recent years, the exact mechanism of MIA is still unclear.

Overall, there is a lack of knowledge regarding which type of music is more effective in MIA in the current literature. The description of recorded music utilized in clinical trials often lacks precision and transparency [16]. Research suggests that the patient's preferred music might be more effective in pain relief than music chosen by someone else, e.g., the researcher [[17], [18], [19]]. However, in clinical practice, allowing patients to choose their preferred music is often not possible, particularly in emergency situations or at the ICU where patients may be sedated. In those situations, health care professionals may make such decisions, reflecting their own tastes and/or in line with widespread beliefs about supposed universally effective types of music. Therefore, to purposefully use music for pain relief, it is essential to investigate the effect of different types of music, such as self-chosen and researcher-chosen music.

Currently, there is no consensus about which music works best for which patient. Previous research investigated the psychophysiological effect of self-chosen music, highlighting the importance of individual preferences [20]. While research on pain (management) is increasingly sensitive for socio-cultural differences [21,22], research on MIA notably lacks consideration for socio-cultural background characteristics such as level of education, age or ethnicity. Sociological studies have established that these characteristics – cultural capital as a trait of level of education most specifically – act as key factors contributing to musical taste differentiation [[23], [24], [25], [26], [27]] and music perception [28,29]. Moreover, these factors affect musical taste patterns, which in turn are closely aligned with listening experience and social identity, in which musical taste plays a significant role as well [30,31]. For example, people who have enjoyed higher education levels are typically much more inclined to like ‘highbrow’ music such as classical or jazz [24,26], which also prescribe different behaviors – e.g. sitting, contemplation, not singing along – during listening and concerts than less ‘legitimate’ music preferences such as rap, schlager or heavy metal [32]. As a consequence, these socio-cultural background characteristics can potentially affect MIA [26,27], which is why this should be considered when investigating the therapeutic effects of music on pain.

This study aims to investigate whether the effect of (preferred) music on pain endurance remains consistent across different socio-cultural backgrounds. With this study, we will combine knowledge from different disciplines by integrating sociological methods into medical research, which could provide new perspectives on music as medicine. The MOSART study adopts a cross-over design, wherein every participant will undergo three distinct interventions in a randomized sequence: 1) self-chosen music, 2) researcher-chosen music, and 3) a neutral spoken-word podcast as a control condition. Following each intervention, participants will be subjected to increasing electric stimuli to assess changes in pain endurance.

This study is a follow-up to a recent experimental study by our research group, in which recorded (preferred) music showed a beneficial effect over a control group with silence [33]. Building on the findings from this previous study, the current research will explore two distinct music interventions and introduce a podcast as a non-music control condition. This approach aims to specifically discern potential differences between (self- or researcher-chosen) music and any form of distraction provided by a cultural product (podcast). In this way, we aim to gain more insight into the working mechanisms of MIA specifically as opposed to other cultural interventions, and pave the way to a more personalized approach in MIA.

## Methods

2

### Study design

2.1

This randomized controlled trial investigates the effect of self-chosen music and researcher-chosen music while considering socio-cultural background. Listening to a neutral, non-musical informative podcast will serve as a non-music control condition. The study will have a Latin-square crossover design to account for individual differences in pain perception and the influence of music. Hence, each participant will receive all three interventions (self-chosen music, researcher-chosen music, and control) in a randomized order. Each intervention has a duration of 20 min, and there will be a 20-min washout period between interventions. In this wash-out period, no music or stressful activities will be allowed. At the end of each intervention, pain endurance by increasing electric stimuli will be tested as the primary outcome of this study. Moreover, physiological assessments, psychological questionnaires – evaluating emotions and anxiety – and a comprehensive survey regarding socio-cultural background will be conducted. Measurements will take place at the outpatient clinic of the Center of Pain Medicine at Erasmus Medical Center, Rotterdam. See Fig. 1 for a comprehensive overview of the study design.

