### Sample size calculation

2.2

As there is currently no published research examining the interaction of music with socio-cultural background in relation to pain sensation, we conducted a power analysis based on the same meta-analysis that was used in the previous trial (CRESCENDo-trial) [5,33]. We estimated a slightly lower effect size (Cohen's d 0,4), considering the utilization of a podcast as a non-music control condition in this study. The intraclass correlation coefficient (ICC) was estimated based on a study that assessed pain intensity and unpleasantness ratings before and after listening to music [17]. To obtain a power of 90 % with a two-sided significance level of 5 % and under consideration of possible dropouts, we calculated that a sample size of 84 was needed. Thus, each group, stratified by level of education, will consist of n = 28.

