#### Pain endurance

2.4.1

The primary outcome of this study is pain endurance, quantified in amperage, through increasing electric stimuli administered at the end of each intervention (self-chosen music, researcher-chosen music, and control). The electric stimuli will be administrated by the STMISOLA (Biopac Systems Inc. Goleta, CA, USA). Two electrodes will be attached to the index finger of the non-dominant hand. Administration of the electrical pulses with a frequency of 100 Hz will start when the participants press a button with the other, dominant hand. When this button is pressed, electric pulses with a current increase rate of 0.5 mA/s will be administered up to a maximum of 30 mA for safety reasons.

When the experiment starts and the participant is connected to the device, the sensation threshold will be tested. At the end of each intervention, while the participants are still listening to music or the podcast, the pain endurance will be tested. Standardized instructions will be used, instructing participants to tolerate the electric pain stimuli as long as possible. Each measurement will be repeated three times, and the average amperages will be registered.

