#### Conceptual basis of time periods used within study design

3.2.2

The length of the (music) listening periods were based on previous clinical and experimental studies [5,33,68]. Although clinical trials show especially high discrepancies in the length of music listening, ranging from 5 to 120 min, the most frequent listening durations last between 15 and 30 min [16,69]. Therefore, we chose to incorporate a 20-min period for all three interventions (self-chosen music, researcher-chosen music and control condition).

The choice of a 20-min wash-out period was grounded in the pharmacokinetics of potential key neurochemicals implicated in MIA. Given the incomplete understanding of the mechanisms underlying MIA, we aimed for the wash-out period to be strategically positioned relative to the half-lives of potential key neurochemicals. Studies have highlighted the involvement of neurotransmitters such as dopamine, beta-endorphin and oxytocin in modulating pain perception in MIA [[70], [71], [72]]. The half-life times of these specific neurotransmitters have a broad range from 1 min to 1.5 h, but predominantly last from a couple of minutes to 20 min [[73], [74], [75]]. By allowing a 20-min wash-out period between the interventions in this study, we aim to minimize carryover effects. This rationale aligns with the principles of crossover study design, facilitating the accurate assessment of treatment effects while controlling for potential confounders and randomization sequence. Additionally, the choice of a 20-min duration aims to balance the need for an adequate wash-out period with considerations for volunteer comfort and study feasibility.

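### The article names a Latin-square crossover without stating the orders; with one three-order square, unequal after-effects of music and podcast would bias the self- versus researcher-chosen contrast.

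*Protocol article*

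**What the plan says.** Section 2.1 (Study design): "The study will have a Latin-square crossover design to account for individual differences in pain perception and the influence of music". It adds that "each participant will receive all three interventions (self-chosen music, researcher-chosen music, and control) in a randomized order" and that "there will be a 20-min washout period between interventions". Neither the number of orders nor a list of sequences is given.

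Section 2.4.1 (Pain endurance) times the primary outcome: "At the end of each intervention, while the participants are still listening to music or the podcast, the pain endurance will be tested".

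Section 3.2.2 supports the washout with neurochemical half-lives that "have a broad range from 1 min to 1.5 h, but predominantly last from a couple of minutes to 20 min". It describes the aim as minimising carry-over and presents the design as "facilitating the accurate assessment of treatment effects while controlling for potential confounders and randomization sequence".

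Section 2.5 lists fixed effects for intervention and position in the sequence (plus background covariates), a possible intervention-by-position interaction, random intercepts and a random time-point effect. It says that period and carry-over effects are thereby considered. It names no term for the preceding intervention.

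**The concern.** A single 3×3 Latin square balances position but not precedence. With an odd number of conditions, one square cannot make every condition follow every other equally often; the pair of mirror squares (six orders, a Williams design) can. Under one square, any after-effect of music falls on only one of the two music arms.

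That matters because section 3.2.1 opposes two scenarios: music matched to personal taste works better, or researcher-chosen music works whatever the listener's taste. The self- versus researcher-chosen contrast bears directly on this, and an allocation artefact there could be read as an effect of preference, or could hide one.

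**Working it through.** **Inputs.** Three interventions, 20-min listening periods and a 20-min washout (2.1); pain test at the end of the listening period (2.4.1); 84 participants and d = 0.4 (2.2: "We estimated a slightly lower effect size (Cohen's d 0,4"; "Thus, each group, stratified by level of education, will consist of n = 28"); half-lives (3.2.2). The after-effect L is assumed: equal for both music types and zero for the podcast.

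**Sample size.** The 84 cannot be reproduced, because neither the ICC nor the dropout rate is given. From n = 2(1−ICC)(1.96+1.28)²/d², inflated for dropout, it is attainable with ICC 0.36 and no dropout, 0.42 and 10%, or 0.49 and 20%. It does not settle the number of orders: 84/3 = 28 and 84/6 = 14, while 28 per stratum divides by neither 3 nor 6.

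**Bias.** Write S, R and P for self-chosen, researcher-chosen and podcast. With complete data and balanced positions, each contrast is a difference of intervention means, so the mean residue carried into each intervention is enough.

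| Orders | S | R | P | S−R | S−P | R−P |
|---|---|---|---|---|---|---|
| S-R-P, R-P-S, P-S-R | 0 | 2L/3 | 2L/3 | −0.67L | −0.67L | 0 |
| Mirror: S-P-R, P-R-S, R-S-P | 2L/3 | 0 | 2L/3 | +0.67L | 0 | −0.67L |
| All six | L/3 | L/3 | 2L/3 | 0 | −0.33L | −0.33L |

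For example, in the first square R is preceded by S twice and comes first once, giving (L + L + 0)/3. S is preceded by P twice and comes first once, giving 0. Least squares with participant, period and intervention effects for 84 participants gives the same figures. If all three conditions leave the same residue, every bias is 0.

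**Does the planned model correct it?** With a random time effect (variance 0.2 assumed) the bias stays at 0.65 to 0.67L. With intervention by position it is 0.667L. A first-order term for the preceding intervention does remove it, at a cost in variance of the contrast:

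- no carry-over term: 2/84 = 0.0238 under either design;
- with the term, three orders: 0.119, a ratio of 5.0;
- with the term, six orders: 0.0298, a ratio of 1.25.

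The adjusted standard error under three orders is therefore √(5.0/1.25) = 2 times that under six.

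**Size of L.** The test falls about 20 + 20 = 40 min after the previous listening ends. Assume a 0.4 SD effect decays exponentially, so L = 0.4 × 0.5^(40/h) for half-life h:

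- h = 5 min: L = 0.002, bias 0.001 SD;
- h = 20 min: L = 0.4 × 0.25 = 0.10, bias 0.07 SD;
- h = 90 min: L = 0.4 × 0.735 = 0.29, bias 0.20 SD.

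With SE = √(2(1−ICC)/84) and an assumed ICC of 0.36 to 0.49, the two-sided 5% test of S versus R would reject falsely in about 8 to 9% of trials at L = 0.10 and about 36 to 43% at L = 0.29.

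**Switching part-way.** The trial status section reports 50 enrolled by March 2024. If 51 follow one square and 33 the mirror, the S−R bias is 0.667L × (51−33)/84 = 0.14L. The carry-over-adjusted variance ratio is about 1.29.

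**The case against.** The article never says that three orders are used. A six-order Williams design for three conditions is itself a pair of Latin squares, so the wording fits it too. Fig. 1 and the full protocol (version 2.1) were not available for this check and may list the sequences. This stands: a reader might infer that the trial uses three orders and therefore has a biased contrast, and the document does not support that.

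The bias also needs music and podcast to leave different residues, and positions 2 and 3 are only two thirds of the data. The article calls half-lives up to 20 min predominant, so 0.07 SD sits at the top of that range and 0.20 SD comes from its tail. Both hypotheses as worded in 3.2.1 concern consistency across backgrounds. If residues are equal across strata and orders are balanced within them, the bias is the same in every stratum and cancels from the intervention-by-education interaction. All of this stands and limits the point.

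Nor do six orders help the music-versus-podcast comparison on average. Under one square the two biases are −0.67L and 0, mean −0.33L; under six, each is −0.33L. This also stands.

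None of it answers the core: the plain reading of the stated label is three orders, and under that reading the model in 2.5 does not deal with carry-over as it says it does.

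**Conclusion.** The point holds conditionally. The article leaves the set of orders open. If a single square is used, the preceding condition is fully confounded with intervention in positions 2 and 3. If, in addition, both music types leave an equal residue L and the podcast none, self-minus-researcher is biased by 0.67L in a direction set by the square, and no term named in 2.5 corrects it. Under the assumed decay this runs from about 0 to about 0.20 SD, against a design effect of 0.4 SD.

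It should not be read as evidence that carry-over exists, that the main music-versus-podcast result is made worse by one square, or that the education interaction is biased.

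**What to change.** In section 2.1, specify all six orders (both Latin squares, a Williams design), randomised within education strata. From the start this would give 14 per order overall and 4 or 5 per order in each stratum of 28.

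- If six orders are already in use, correct the label only.
- If one square has been used so far, assign the remaining participants to the three mirror orders. The 14 per order is then out of reach, but a split of about 51/33 cuts the self-versus-researcher bias from 0.67L to 0.14L and the adjusted variance ratio from 5 to about 1.29. Keep the planned model as primary and report a sensitivity analysis with a first-order term for the preceding intervention.
- If enrolment is complete, state the orders used and report that sensitivity analysis.

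The cost is a change to the allocation list, with no added participants, visits or procedures. Made mid-trial, it partly confounds the set of orders with calendar time. Six orders alone still leave a 0.33L bias against music in each music-versus-podcast contrast, which only the carry-over term removes.

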**Fig. 1 fig1:**
[figure not shown]
Flow diagram of the MOSART study design Note: HRV=Heart Rate Variability, NRS=Numeric Rating Scale, STAI= State-Trait Anxiety Inventory, SAM=Self-Assessment Manikin.

### Sample size calculation

2.2

As there is currently no published research examining the interaction of music with socio-cultural background in relation to pain sensation, we conducted a power analysis based on the same meta-analysis that was used in the previous trial (CRESCENDo-trial) [5,33]. We estimated a slightly lower effect size (Cohen's d 0,4), considering the utilization of a podcast as a non-music control condition in this study. The intraclass correlation coefficient (ICC) was estimated based on a study that assessed pain intensity and unpleasantness ratings before and after listening to music [17]. To obtain a power of 90 % with a two-sided significance level of 5 % and under consideration of possible dropouts, we calculated that a sample size of 84 was needed. Thus, each group, stratified by level of education, will consist of n = 28.

### Procedures

2.3

#### Stratification and randomization

2.3.1

Current sociological literature provides evidence that humans are differently socialized regarding music taste and music perception [[23], [24], [25], [26], [27],[34], [35], [36]]. Stratified recruitment and randomization (Castor EDC, Ciwit B·V., Amsterdam) based on level of education will be performed to ensure maximum variation in educational levels in our sample. Since level of education is a key indicator of cultural capital [37], which in turn plays a significant role in shaping individual musical preferences, stratification will be based on participants’ level of education [34]. Thus, the study population will consist of 1/3 less-educated, 1/3 medium-educated, and 1/3 more-educated female subjects. This categorical strategy was chosen because other groupings, such as years of education, are less suitable in the Dutch education system, where students are separated into different educational tracks at the age of 12. A comparison between these three categories will allow us to compare participants belonging to clearly defined educational groupings and thus assess the impact of schooling level as a proxy for cultural capital. An overview of the stratification strategy by level of education can be found in Appendix A.

#### Exclusion and inclusion criteria

2.3.2

Heterogeneity in pain tolerance is partly linked to gender and age [38,39]. Therefore, including only female subjects between the ages of 18 and 60 years will create a more homogenous study population. The upper age limit of 60 years also aligns with the observation that responsiveness in autonomic activity significantly decreases in the elderly, which could influence Heart Rate Variability (HRV) measurements [40,41]. Furthermore, the usage of analgesic medication within the last 24 h and/or chronic and acute pain conditions were exclusion criteria in this study. A full overview of the in- and exclusion criteria can be found in Table 1.

**Table 1 tbl1:** Overview of the eligibility criteria.

Inclusion criteria	Exclusion criteria
• Between 18 and 60 years of age	• Significant hearing impairment
• Female	• Current complaints of tinnitus
• Sufficient knowledge of the Dutch language	• Current treatment by a medical specialist or general practitioner
• Provision of written informed consent	• Current use of analgesic medication
	• Presence of acute or chronic pain
	• History of cardiac disease of arrhythmias
	• Electric implants (e.g. pacemakers)
	• Diagnosed psychiatric or neurological impairments
	• (Suspected) pregnancy

